## Abstract

**Background:**

Osteosarcoma is the most common primary malignant bone tumor in children and adolescents. For effective treatment, local control of the tumor is absolutely critical, because the chances of long term survival are <10% and might effectively approach zero if a complete surgical resection of the tumor is not possible. Up to date there is no curative treatment protocol for patients with non-resectable osteosarcomas, who are excluded from current osteosarcoma trials, e.g. *EURAMOS1*. Local photon radiotherapy has previously been used in small series and in an uncontrolled, highly individualized fashion, which, however, documented that high dose radiotherapy can, in principle, be used to achieve local control. Generally the radiation dose that is necessary for a curative approach can hardly be achieved with conventional photon radiotherapy in patients with non-resectable tumors that are usually located near radiosensitive critical organs such as the brain, the spine or the pelvis. In these cases particle Radiotherapy (proton therapy (PT)/heavy ion therapy (HIT) may offer a promising new alternative. Moreover, compared with photons, heavy ion beams provide a higher physical selectivity because of their finite depth coverage in tissue. They achieve a higher relative biological effectiveness. Phase I/II dose escalation studies of HIT in adults with non-resectable bone and soft tissue sarcomas have already shown favorable results.

**Methods/Design:**

This is a monocenter, single-arm study for patients ≥ 6 years of age with non-resectable osteosarcoma. Desired target dose is 60-66 Cobalt Gray Equivalent (Gy E) with 45 Gy PT (proton therapy) and a carbon ion boost of 15-21 GyE. Weekly fractionation of 5-6 × 3 Gy E is used. PT/HIT will be administered exclusively at the Ion Radiotherapy Center in Heidelberg. Furthermore, FDG-PET imaging characteristics of non-resectable osteosarcoma before and after PT/HIT will be investigated prospectively. Systemic disease before and after PT/HIT is targeted by standard chemotherapy protocols and is not part of this trial.

**Discussion:**

The primary objectives of this trial are the determination of feasibility and toxicity of HIT. Secondary objectives are tumor response, disease free survival and overall survival. The aim is to improve outcome for patients with non-resectable osteosarcoma.

**Trail Registration:**

Registration number (ClinicalTrials.gov): NCT01005043

## Background

Osteosarcoma is the most common primary malignant bone tumor in children and adolescents but also occurs in adults. The most frequent primary tumor sites are the distal femur and the proximal tibia, but there are a significant number of patients with axial primary tumors or other unfavorable, non-resectable tumor sites (5-10%). Effective treatment depends on neoadjuvant and adjuvant chemotherapy to control micrometastatic disease, and on radical surgical resection to control the primary tumor. Local control of the tumor is absolutely critical, because the chances of long term survival are <10%, if a complete surgical resection of the tumor is not possible [1,2]. In a minority of patients, the tumor cannot be completely resected without unacceptable mutilation. In such patients local radiotherapy has previously been used. Published small series of such patients have documented that radiotherapy can achieve local control [3], although the success rate of this strategy has not been analyzed in systematic trials.

Although the small series of patients with non-resectable tumors, who received local radiotherapy but no surgery showed encouraging results, the necessary high radiation doses cannot be achieved in many patients with tumors near critical organs such as the brain, the spinal cord or small bowel. In such cases PT plus HIT may offer a promising alternative.

Compared with photons, heavy ion particles such as carbon ions or protons provide a higher physical selectivity because of their finite depth coverage in tissue and, in the case of heavy ions, achieve a higher relative biological effectiveness. Phase I/II dose escalation studies of HIT in adults with non-resectable bone and soft tissue sarcomas showed favorable results [4,5]. Kamada et al. demonstrated a 3-year overall survival rate of 45% in a series of 15 patients with non-resectable osteosarcoma of the pelvis (10 patients) or the spine (5 patients). These results are clearly superior to most published 3-year survival rates in patients with non-resectable osteosarcoma of the pelvis and/or spine, who did not receive radiotherapy [6,7].

Since 1997, HIT is available for the treatment of patients at the Gesellschaft für Schwerionenforschung (GSI) in Darmstadt, Germany. Up to now, more than 400 patients with various tumor types were successfully irradiated at the GSI [8,9]. From November 2009, HIT and PT will be available at the University of Heidelberg. In contrast to other centers, the facility at Heidelberg relies on active beam delivery using the so called raster scan technique, which offers physical advantages with better sparing of normal tissue in the entrance channel, less scattering dose. Furthermore, biological plan optimization is performed.

This study aims at improving outcome in patients with non-resectable osteosarcoma

## Methods/Design

### Study design

The study is designed as a mono center, single arm phase I/II pilot trial.

### Study objectives

The primary objective is to evaluate the feasibility and toxicity of dose escalation via PT/HIT in patients with osteosarcoma. Secondary objectives are the evaluation of tumor response, disease free survival, overall survival and description of FDG-PET characteristics in patients with osteosarcoma before and after PT/HIT in order to evaluate prospectively the association between FDG-PET and survival respectively time to progression.

### Trial organization

The trial has been designed by the study initiators at the Department of Radiation Oncology and the Department of Pediatric Oncology, Hematology, Immunology and Pneumology. The trial is carried out by the Department of Radiation Oncology and the Department of Pediatric Oncology, Hematology, Immunology and Pneumology at the University of Heidelberg.

### Coordination

The overall coordination is performed by the Department of Radiation Oncology at the University of Heidelberg. This department is responsible for the overall trial management, database management, quality assurance including monitoring and reporting.

### Investigators

The study investigators are experienced radiation oncologists respectively pediatricians. Patients will be treated by the physicians of the Department of Radiation Oncology and the Department of Pediatric Oncology, Hematology, Immunology and Pneumology.

### Ethics, informed consent and safety

The final protocol was approved by the ethics committee of the University of Heidelberg, Heidelberg, Germany (Nr. S-153/2008). This trial complies with the Helsinki Declaration in its recent German vision, the medical Association code of conduct, the principles of Good Clinical Practice (GCP) and the Federal Data Protection Act. The study will also be carried out in keeping with local legal and regulatory requirements. It is subjected to authorization by the "Bundesamt für Strahlenschutz". The medical secrecy and the Federal Data Protection Act will be followed.

### Patient selection

The following inclusion criteria must be fulfilled:

▪ Histological diagnosis of high grade osteosarcoma with or without metastases

▪ **Non-resectable* **tumor of the pelvis, the skull base or the spine, respectively, incomplete or intralesional tumor resection - as confirmed after evaluation by two orthopedic surgeons (respectively neurosurgeons in case of spine tumors): one local surgeon and one referee surgeon of the University of Heidelberg.

▪ Age ≥ 6 years before start of radiotherapy

▪ Adequate performance status (Karnofsky ≥ 60%)

▪ Adequate blood cell production before the start of PT/HIT in patients with pelvic or spine tumors as defined by: total white cell count (WBC) ≥ 1,0/nl; neurophils ≥ 200/μl; platelet count ≥ 20/nl

▪ No febrile neutropenia (neutrophils < 200/μl)

▪ Written informed consent of the patient or the legal guardians

*Non-resectable tumor site means primary tumors affecting anatomic areas of the human body where a surgical total resection (R0) of the tumor is not possible for technical reasons, for example osteosarcoma of the pelvis, spine or the skull base. In any other cases, surgical resection is recommended.

Non-resectability has to be confirmed after evaluation by two orthopedic surgeons (respectively neurosurgeons in case of spine tumors): one local surgeon and one referee surgeon of the University of Heidelberg.

In some cases surgery of the tumor might be possible after PT/HIT. Than we recommend surgical resection of residual tumor afterwards.

### Exclusion criteria

▪ Age < 6 years

▪ Previous radiotherapy of the field that has to be radiated now

▪ Implanted metal within the planned radiation field, that leads to significant artefacts within the target volume

▪ Patients receiving any other investigational agents during the time of HIT

▪ Performance status (Karnofsky) ≤ 60%)

▪ Pregnancy

▪ No written informed consent of patient or the legal guardians

### Statistical calculations for trial sample size

20 patients ≥ 6 years will be included in the trial. This number ensures acceptable 95%-confidence intervals for the description of incidence of toxicities as well as for the efficacy of the HIT-treatment in this trial. For response rates of 30% the 95%-confidence interval will be 17.9-44.6%.

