### Time plan for the study

The study will be started in January 2010. Patient recruitment will be completed when 20 patients are included which is expected latest in 2015. Patient follow-up will continue for at least 5 years within our center, and will continue on a regular written basis (once yearly). The trial will be completed latest in 2020.

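### The 95% confidence interval given to justify 20 patients (17.9-44.6% at 30% response) is not the interval for 20 patients; it matches the exact interval for 15 of 50

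*Protocol article*

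**What the plan says.** The section on statistical calculations for trial sample size fixes the number: "20 patients ≥ 6 years will be included in the trial". It then says what that number achieves: "This number ensures acceptable 95%-confidence intervals for the description of incidence of toxicities as well as for the efficacy of the HIT-treatment in this trial". One numerical illustration follows: "For response rates of 30% the 95%-confidence interval will be 17.9-44.6" per cent. No interval method is named.

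The Time plan section repeats the same number as the end of accrual: "Patient recruitment will be completed when 20 patients are included". The Study design section confirms that there is only one group: "The study is designed as a mono center, single arm phase I/II pilot trial". No other sample size appears anywhere in the article.

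**The concern.** The interval looks too narrow for 20 patients. At n = 20 and a proportion of 0.30 the standard error is √(0.30 × 0.70 / 20) = 0.102, so even the simplest 95% interval reaches about 20 points either side of 30%. The printed limits lie only 12.1 points below and 14.6 points above.

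The sample size rests on no hypothesis test or power calculation. It rests on precision alone, and this interval is the only precision figure given. If it belongs to a larger sample, readers and ethics reviewers have been told that 20 patients deliver a precision they cannot deliver. The judgement that the precision is acceptable was then supported by the wrong number. The same paragraph extends that judgement to toxicity, a primary objective, for which no interval is shown.

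**Working it through.** **Inputs**
- n = 20, single arm (sample size, Time plan and Study design sections).
- Response rate 30%, so x = 0.30 × 20 = 6 exactly; rounding of the count plays no part.
- Confidence 95%, taken as two-sided because both limits are given (z = 1.96).
- Stated interval 17.9-44.6%, width 44.6 − 17.9 = 26.7 points.

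**Attempt to reproduce the stated figure at n = 20**

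*Exact (Clopper-Pearson).* The lower limit is the 2.5% quantile of Beta(x, n − x + 1) and the upper limit the 97.5% quantile of Beta(x + 1, n − x). For 6/20 these are Beta(6, 15) and Beta(7, 14), giving 11.89-54.28%.

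*Wald.* p ± z√(p(1 − p)/n) = 0.30 ± 1.96 × 0.1025 = 0.30 ± 0.201, giving 9.9-50.1%.

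*Wilson.* The centre is (x + z²/2)/(n + z²) = 7.921/23.84 = 0.3322. The half-width is z√(np(1 − p) + z²/4)/(n + z²) = 1.96 × √(4.2 + 0.960)/23.84 = 0.1868. This gives 14.5-51.9%.

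All 95% methods tried for 6/20:

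| Method | Interval (%) |
|---|---|
| Clopper-Pearson | 11.9-54.3 |
| Wald | 9.9-50.1 |
| Wald, continuity-corrected | 7.4-52.6 |
| Wilson | 14.5-51.9 |
| Wilson, continuity-corrected | 12.8-54.3 |
| Agresti-Coull | 14.3-52.1 |
| Jeffreys | 13.6-51.7 |
| mid-P | 13.2-52.3 |

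Every lower limit is below 15% and every upper limit is above 50%. None is near 17.9-44.6%.

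**Could a different confidence level explain it?** At 90%, 6/20 gives 14.0-50.8% (exact) and 16.4-48.4% (Wilson). At 80% it gives 16.6-46.7% (exact) and 18.8-44.2% (Wilson). None matches. An exact interval at n = 20 gets close to the printed limits only at about 73% confidence (18.0-44.7%).

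**Which sample does give the stated figure?** A search over n = 10 to 120 covered observed proportions between 20% and 42%, five methods (Clopper-Pearson, Wald, Wilson, Agresti-Coull, Jeffreys) and three levels (95%, 90%, 80%). It returned one match: 15/50, exact, 95%. The quantiles of Beta(15, 36) and Beta(16, 35) give 17.86-44.61%, which rounds to 17.9-44.6%.

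**Size of the discrepancy.** The exact width for 6/20 is 54.28 − 11.89 = 42.39 points. The ratio to the stated width is 42.39/26.7 = 1.59. Even Wilson, the narrowest of the 95% methods above, is 51.90 − 14.55 = 37.35 points wide, and 37.35/26.7 = 1.40.

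**Toxicity, for scale.** With no events in 20 patients the exact two-sided 95% upper limit is 1 − 0.025^(1/20) = 16.8%. With 1/20 the exact interval is 0.1-24.9%. The Adverse events section treats rates above grade 3 of at most 5% (acute) and at most 3% (late) as acceptable.

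**The case against.** The best defence concerns weight, not arithmetic. Response is a secondary objective in a pilot trial whose primary objective is feasibility and toxicity. No test, stopping boundary or go/no-go rule in the article uses the response interval, and correcting it changes no endpoint or eligibility criterion. This stands: the error does not invalidate a descriptive pilot. But the figure remains the only quantitative support for the sample size, and it errs in the favourable direction.

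A second point is that the link to 50 patients is a numerical match, not documented history. That also stands. The uniqueness of the match also depends on the search grid: a 99% Wald interval for 25/80 rounds to the same limits. That case has neither the stated 95% level nor a 30% rate, so it does not help the plan. The conclusion does not need the origin of the figure, only that it is not a 95% interval for 6/20.

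Finally, an article condenses a fuller protocol. That can excuse an omission, but not a printed figure that contradicts the sample size printed beside it.

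**Conclusion.** The concern holds. The stated interval is wrong for the planned sample and overstates precision. At 30% response the exact 95% interval with 20 patients is 11.9-54.3%, a width of 42.4 points against the 26.7 printed, or about 59% wider. If 6 of 20 respond, the data would be compatible with true rates from roughly 12% to just above 50%.

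This rests on n = 20, exactly 6 responders, all 20 patients evaluable, and a two-sided 95% level. The choice of method moves the limits by a few points but does not rescue the stated figure. The statement that 20 patients ensure acceptable intervals has no correct number behind it as written.

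**What to change.** First confirm that 20 is the intended sample size.

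- If it is, replace the interval with one for 20 patients and name the method, for example: *With 20 patients and 6 responses (30%), the exact (Clopper-Pearson) 95% confidence interval is 11.9-54.3%.* Then state whether that precision is still considered acceptable, because that judgement was made beside a narrower interval. Another standard method may be used if it is named.
- If 20 is not the intended number, correct it in both the sample size and Time plan sections.

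It would also help, though it is optional, to describe the response estimate as exploratory and to give an interval for toxicity at the same sample size (for example 0-16.8% for 0/20), since the paragraph claims acceptable precision there too.

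If 20 is kept, the cost is one corrected sentence and a less favourable statement of precision, with no extra patients and no change to the conduct of the trial.

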### Adverse events

Radiotherapy-related toxicities will be assessed using the NCI Common Terminology Criteria (CTC). Toxicity will be evaluated pre-treatment, weekly during radiation therapy (blood count, electrolytes, chemistry, clinical examination, patient visits) and at follow-up (1 week, 6 and 19 weeks, 6, 12, 24, 36 48 and 60 months after PT/HIT). Unacceptable toxicity is defined as unpredictable or irreversible grade 4 toxicity.

Expectable possible acute toxicities (up to 3 months post PT/HIT) are

- Depression of hematopoesis

- Mucosa: ulcera, chronic inflammation, colic, diarrhoea, bowel stenosis, urinary bladder inflammation, contracted bladder

- Skin: erythema, epitheliolysis

- CNS: sickness, vomiting, central nerve palsy, elevated intracranial pressure, headach, dizziness

- sceletal system: necrosis, fracture, joint dysfunction, disturbance of growth

Late effects are rare and defined as symptoms appearing at least 3 months post irradiation. These could include:

- Bowel stenosis or perforation with need for surgical intervention

- Chronic bowel inflammation

- CNS: central nerve palsy, cerebral palsy, impaired vision, defective hearing (very rare)

- Disturbance of growth

- Secondary malignancies: The incidence of secondary malignancies is possibly increased by high-LET radiotherapy like HIT

- arteriosclerosis

- Incontinence (very rare)

- Impotence (very rare)

A rate of acute toxicity (≤ 3 months during respectively after PT/HIT) > grade 3 of ≤ 5% and a rate of late toxicity (after ≥ 3 months) > grade 3 of ≤ 3% will be regarded as acceptable.

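### With 20 patients, meeting the 5% acute and 3% late toxicity limits cannot show that the true rates lie within them, and the sample-size section claims adequate precision without showing a toxicity interval

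*Protocol article*

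**What the plan says.** The Study objectives section of the protocol article states: "The primary objective is to evaluate the feasibility and toxicity of dose escalation via PT/HIT in patients with osteosarcoma". The Study design section adds: "The study is designed as a mono center, single arm phase I/II pilot trial".

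The Adverse events section sets two numeric limits. The acute one is "A rate of acute toxicity (≤ 3 months during respectively after PT/HIT) > grade 3 of ≤ 5" per cent; the late one reads "a rate of late toxicity (after ≥ 3 months) > grade 3 of ≤ 3% will be regarded as acceptable". The same section separately defines unacceptable toxicity as grade 4 toxicity that either could not be foreseen or does not reverse. Neither statement is given an event count, a denominator, an estimator, a confidence bound or an error rate.

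The sample-size section says "20 patients ≥ 6 years will be included in the trial" and justifies the number so: "This number ensures acceptable 95%-confidence intervals for the description of incidence of toxicities". It prints no interval for any toxicity rate. Its one worked interval is for response: "For response rates of 30% the 95%-confidence interval will be 17.9-44.6" per cent.

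Toxicity is assessed before and during treatment and "at follow-up (1 week, 6 and 19 weeks, 6, 12, 24, 36 48 and 60 months after PT/HIT").

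**The concern.** An observed rate in 20 patients moves in steps of 5 percentage points. A 5% limit therefore sits on the first step, and a 3% limit falls between zero and the first step. The late limit is in effect a requirement of no events, which the article does not say.

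The verdict of acceptability is attached to a primary objective, in a trial that admits children from age 6 and whose Discussion concedes that little is known about side effects of heavy ion therapy in children. A reader who sees that the limits were met, and has been told that 20 patients give acceptable intervals, may take this as evidence that severe toxicity truly occurs in at most 5% and 3% of patients. The opposite error is also possible: a treatment that does satisfy the limits may miss them through one or two chance events.

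**Working it through.** **Inputs.** n = 20 (sample-size section); limits of 5% acute and 3% late for toxicity above grade 3 (Adverse events); 95% confidence (sample-size section). Assumption: each limit is compared with the crude proportion of 20 evaluable patients who have an event.

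**The article's own interval.** For a 30% rate in 20 patients (6/20), the exact (Clopper-Pearson) 95% interval is 11.9-54.3%; Wald gives 9.9-50.1% and Wilson 14.5-51.9%. None is the printed 17.9-44.6%. The exact interval for 15/50 is 17.86-44.61%, so the printed figure matches 50 patients. This is a separate error, but it means that the only figure offered for the precision of n = 20 does not describe n = 20.

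**Limits as counts.**
- Acute: 20 × 0.05 = 1.0, so at most 1/20.
- Late: 20 × 0.03 = 0.6, so 0/20; one event is 1/20 = 5%, above 3%.

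**Exact intervals for the largest count allowed.**
- 0/20, two-sided 95%: upper limit 1 − 0.025^(1/20) = 16.8%. One-sided 95%: 1 − 0.05^(1/20) = 13.9%.
- 1/20, two-sided 95%: the lower limit solves 1 − (1 − p)^20 = 0.025, giving 0.1%; the upper limit solves (1 − p)^20 + 20p(1 − p)^19 = 0.025, giving 24.9%. One-sided 95% (0.05 on the right-hand side): 21.6%.

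The two-sided upper limits are about five times the acceptance limits: 24.9/5 = 5.0 and 16.8/3 = 5.6.

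**Probability of meeting each limit.** Acute: P(X ≤ 1) = (1 − p)^20 + 20p(1 − p)^19. Late: P(X = 0) = (1 − p)^20.

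| True rate | Rule | Calculation | P(limit met) |
|---|---|---|---|
| 5% (at limit) | acute ≤ 1/20 | 0.358 + 0.377 | 0.74 |
| 10% (twice) | acute ≤ 1/20 | 0.122 + 0.270 | 0.39 |
| 3% (at limit) | late 0/20 | 0.97^20 | 0.54 |
| 6% (twice) | late 0/20 | 0.94^20 | 0.29 |

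If the two outcomes were independent, a treatment exactly at both limits would meet both with probability 0.736 × 0.544 = 0.40.

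**Size needed for a bound at the limit, with zero events.** n = ln(α)/ln(1 − limit), rounded up. One-sided 95% (α = 0.05): 59 for 5% and 99 for 3%. Two-sided 95% (α = 0.025): 72 and 122. These show the scale of the gap; they are not a proposal.

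**If fewer than 20 are evaluable (assumed range).** 0/15 gives a two-sided upper limit of 21.8% and 0/10 gives 30.8%. One acute event in 19 is 1/19 = 5.3%, so the acute limit would then also allow no event.

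**The case against.** The strongest reply is that this is a pilot sized to describe toxicity, not to test it. The article nowhere says that the trial will demonstrate a true rate below 5% or 3%, or that the treatment is rejected otherwise. That stands. A reader might infer that the limits cannot be used at all with 20 patients; the text does not support this, because an observed rate can be compared with a benchmark. What remains is that the article attaches a verdict to the benchmark and claims adequate precision for it.

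A second reply is that the estimator is left open, and with follow-up to 60 months a time-to-event estimate may be specified in the full protocol or SAP, which are not shown. The count reading is therefore labelled as an assumption. A Kaplan-Meier risk would not rescue the late limit: a single event with r patients at risk contributes 1/r, and r ≤ 20 gives at least 5%. A rate per person-year would be a different quantity, but the article gives no time unit.

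Third, a reader might take the two limits as the trial's only toxicity criterion. They are not, since the same section also defines unacceptable toxicity. Nor do the limits amount to a stopping rule: the article attaches no consequence for accrual, and none is proposed here. A trigger at the first breach would fire in about 1 − 0.40 = 60% of trials of a treatment exactly at both limits (if independent), and would presume that toxicity is known before the next patient enters.

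Finally, recruiting 20 patients is expected to take from 2010 to as late as 2015, so 59 to 122 patients is not realistic. That also stands, and the point does not depend on a larger trial.

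**Conclusion.** The point holds as one of interpretation and stated precision, not as a fault in choosing 20 patients. Under crude proportions of 20 evaluable patients, the limits permit at most one acute and no late event above grade 3. Even then, true rates up to about 25% (acute) and 17% (late) remain inside the two-sided 95% intervals; on a one-sided 95% basis the figures are about 22% and 14%, and the conclusion is the same. The comparison errs noticeably in both directions: a treatment exactly at a limit misses it with probability 0.26 (acute) or 0.46 (late), while one at twice the limit meets it with probability 0.39 or 0.29.

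The statement that 20 patients ensure acceptable toxicity intervals is unsupported for any use in which the intervals must inform limits of 5% and 3%. Fewer evaluable patients would widen the bounds. A reader might infer that the design must be enlarged or that the treatment would be wrongly licensed by a formal test; the article sets up no such test, so neither follows.

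**What to change.** 1. In Adverse events, express each limit as an event count with the evaluable denominator for its window, and say plainly that a 3% late limit allows no event in 20 or fewer patients.
2. In the sample-size section, replace the claim of acceptable toxicity intervals with the exact n = 20 intervals (0/20: 0-16.8%; 1/20: 0.1-24.9%) and the pass probabilities (0.74 and 0.54 at the limits; 0.39 and 0.29 at twice the limits).
3. Report the exact interval beside any verdict of acceptability, and limit the conclusion to: observed rate within the limit; true rates up to about 17% (late) or 25% (acute) not excluded. If fewer than 20 patients are evaluable, recalculate the bounds for that number.
4. Reconcile the limits with the definition of unacceptable toxicity in the same section. As written, one irreversible grade 4 acute event is 1/20 = 5%, which satisfies the acute limit and yet meets that definition. Which should prevail is for the investigators.

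The cost is a few sentences, a less favourable statement of precision and a more modest safety conclusion. No patients are added.
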